### **10.3 Safety analysis**

The safety analysis is evaluated by a summary of TEAE, changes in laboratory test results, ECG or cardiotoxicity evaluation indicators and changes in vital signs among the specific population.

Adverse events will be summarized according to the Medical Dictionary for Regulatory Activities (MedDRA, version 19.1) and displayed in accordance with the system organ classification and selected terminology. At the same time, the relevance

between SAE and AE, the severity of AE and a summary of some special events are listed separately.

Changes in laboratory test results will be summarized according to the NCI-CTCAE (version 5.0). For laboratory indicators, the maximum toxicity that occurred during the study period is summarized in the form of counts and percentages. The changes in vital signs and ECOG scores will be compared with baseline levels and carried out descriptive statistics. A summary of vital signs, ECG, laboratory and physical examination will be given in a chronological order.

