|  | 
 
i. Absolute neutrophil count <math>\geq 1.5 \times 10^9 / L</math> for subjects without marrow involvement of lymphoma; absolute neutrophil count <math>\geq 1.0 \times 10^9 / L</math> for subjects with marrow involvement;
 
ii. Hemoglobin <math>\geq 90 \text{ g/L}</math> (without red blood cell infusion within 14 days), hemoglobin <math>\geq 75 \text{ g/L}</math> for subjects without marrow involvement of lymphoma;
 
iii. Platelet count <math>\geq 75 \times 10^9 / L</math> for subjects without marrow involvement of lymphoma; platelet count <math>\geq 50 \times 10^9 / L</math> for subjects with marrow involvement;
 
iv. Upper Limit Normal (ULN), or creatinine clearance (<math>\geq 40 \text{ mL/min}</math>) of serum creatinine (<math>\leq 1.5</math> times normal value upper limit) (estimated by the Cockcroft-Gault formula);
 
v. Serum total bilirubin <math>\leq 1.5</math> times ULN;
 
vi. Aspartate Aminotransferase (AST), Alanine Aminotransferase (ALT) <math>\leq 2.5</math> times ULN;
 
vii. Coagulation function: International Normalized Ratio (INR) <math>\leq 1.5</math> times ULN; Prothrombin Time (PT), Activated Partial Thromboplastin Time (APTT) <math>\leq 1.5</math> times ULN (unless the
 
 |

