## **4. Patient selection**

### **4.1 Inclusion criteria**

1. Subjects who have fully understood the study and have signed the informed consent form (ICF).
2. Male or female, age over 18 years (including 18) old and no more than 75 years old.
3. Extranodal NK/T-cell lymphoma confirmed by histopathology examination.
4. Refractory and relapsed ENKTCL that has failed the treatment of asparaginase-based chemotherapy or radiochemotherapy.

Definition of refractory:

- i. Failure to get PR after chemotherapy with asparaginase-containing regimen;  
or

- ii. Disease progression within 6 months of the final asparaginase-containing regimen.
5. Subjects with Eastern Cooperative Oncology Group (ECOG) performance status score of 0 or 1;
  6. The expected survival time is over 3 months.
  7. There must be at least 1 evaluable or measurable lesion that meets the RECIL 2017 lymphoma criteria [evaluable lesion: 18F-Fluorodeoxyglucose/Positron Emission Tomography (18F-Fluorodeoxyglucose/Positron Emission Tomography, 18FDG/PET) examination showing increased lymph nodes or extranodal uptake (higher than liver) and PET and/or Computed Tomography (CT) features are consistent with lymphoma manifestations; measurable lesions: nodular lesions longer than 15mm or extranodal lesions longer than 10mm (if the only measurable lesion has received radiotherapy in the past, there must be evidence of radiological progression after radiotherapy) and accompanied by increased 18FDG uptake]. Except for this, there is no measurable increase in the diffuse 18FDG uptake in the liver.
  8. Subjects should have adequate hematological, hepatic, and renal function as defined by the following laboratory examinations. Subjects have not received cell growth factors, platelet or granulocyte infusion within 7 days before hematological examinations (for the long-acting granulocyte-colony stimulating factor [G-CSF] and [PEG-CSF], the interval of 2 weeks is required):
    - a) Absolute neutrophil count  $\geq 1.5 \times 10^9$  / L for subjects without marrow involvement of lymphoma; absolute neutrophil count  $\geq 1.0 \times 10^9$  / L for subjects with marrow involvement;
    - b) Hemoglobin  $\geq 90$  g/ L (without red blood cell infusion within 14 days),

- hemoglobin  $\geq 75$  g/L for subjects without marrow involvement of lymphoma;

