- c) Platelet count  $\geq 75 \times 10^9$  / L for subjects without marrow involvement of lymphoma; platelet count  $\geq 50 \times 10^9$  / L for subjects with marrow involvement;
  - d) Upper Limit Normal (ULN), or creatinine clearance ( $\geq 40$  mL/min) of serum creatinine ( $\leq 1.5$  times normal value upper limit) (estimated by the Cockcroft-Gault formula);
  - e) Serum total bilirubin  $\leq 1.5$  times ULN;
  - f) Aspartate Aminotransferase (AST), Alanine Aminotransferase (ALT)  $\leq 2.5$  times ULN;
  - g) Coagulation function: International Normalized Ratio (INR)  $\leq 1.5$  times ULN; Prothrombin Time (PT), Activated Partial Thromboplastin Time (APTT)  $\leq 1.5$  times ULN (unless the subject is receiving anticoagulant therapy and PT and APTT are using anticoagulant therapy at the screening time).
  - h) Thyroid-stimulating hormone (TSH) or free thyroxine (FT4) or free triiodothyronine (FT3) are all within the normal range ( $\pm 10\%$ ).
9. There was no evidence that subjects had difficulty breathing at rest, and the measured value of pulse oximetry at rest was more than 92%;
10. Subjects must pass a pulmonary function test (PFT) to confirm that forced expiratory volume (FEV1)/forced vital capacity (FVC) in the first second is more than 60%, unless it is a large mediastinal mass caused by lymphoma that cannot meet this standard; carbon monoxide diffusion (DLCO), FEV1 and FVC are all above 50% of the predicted value; all PFT results must be obtained within four weeks before the first administration;

11. Subjects who have received anti-tumor therapy should be screened only after the toxicity of the previous treatment has recovered to the grade 1 level or baseline level according to Common Terminology Criteria for Adverse Events (CTCAE) V5.0;
12. Women of Childbearing Potential (WOBCP) must undergo a serum pregnancy test within seven days before the first medication and the results are negative. WOBCP or men and their WOBCP partners should agree to take effective contraceptive measures from the signing of ICF until six months after the last dose of the research drug is used.

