## **8 Safety assessment**

### **8.1 Safety Endpoint**

Safety monitoring begins when the ICF is signed and continues until 4 weeks after the end of treatment or until the beginning of another anti-tumor treatment (whichever occurs first). The safety endpoints of this study are as follows:

- The incidence, type and severity of adverse events during treatment are classified according to NCI-CTCAE (version 5.0). Research-related TEAE, SAE, Grade 3 or higher non-hematological AE, Grade 4 hematological AE and permanent discontinuation due to TEAE.
- The frequency and causes of deaths that occurred within 4 weeks ( $\pm 3$  days) of the last medication.
- Safety laboratory inspections classified according to NCI-CTCAE (version 5.0).
- Vital signs, ECG, full physical examination and ECOG physical status score.

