## 8.2 Evaluation of Adverse Events

### 8.2.1 Definition of adverse events

Adverse events refer to any adverse medical events that occur after exposure to a drug (including research drugs) while not necessarily have a causal relationship with the treatment. Therefore, AE can be any unfavorable and unexpected signs (including abnormal laboratory test results), symptoms or diseases temporally correlated to medication regardless of whether it is causally related to the treatment.

Adverse events during treatment refer to AEs that occurred after the first administration of research drugs.

**Note:** AE can therefore refer to any unfavorable and unexpected signs (including abnormal laboratory test results), symptoms or diseases (new or worsening) temporally correlated to medication. For marketed drugs, it also includes failure to obtain the expected benefits, abuse or misuse.

Events that meet the AE definition include:

1. Exacerbation of pre-existing chronic or intermittent diseases, including increased frequency and/or severity.
2. A newly discovered or diagnosed disease after the trial treatment, although the disease may have existed before the start of the study.
3. Suspected signs, symptoms or clinical sequelae of drug interactions.
4. Suspected signs, symptoms or clinical sequelae of trial treatment or concomitant overdose (overdose itself will not be reported as AE/SAE).
5. "Lack of efficacy" or "failure to achieve the expected pharmacological effect" itself is not reported as an AE or SAE. However, any signs and symptoms and/or clinical sequelae caused by "lack of efficacy" will be reported as an AE or SAE if they meet the corresponding definition.

Events that do not meet the definition of AE include:

1. Internal medicine or surgery (for example, endoscopy and appendectomy) while the conditions leading to the above surgery are determined as AEs.
2. The absence of adverse medical events (social and/or environmental facilitating admission).
3. Pre-existing disease or condition at the beginning of the study, with predictable fluctuations that did not aggravate during the study period.
4. The studied disease/abnormality or the expected progression, signs or symptoms of the disease/abnormality under study, unless it is more severe than expected.
5. The collection of AE should start from signing the informed consent form until 30 days after the medication.

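### Section 10.3 announces laboratory changes but counts only the maximum CTCAE grade, so on a literal reading a stable entry abnormality appears as a toxicity

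*Protocol*

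**What the plan says.** Section 10.3 opens its laboratory paragraph with "Changes in laboratory test results will be summarized according to the NCI-CTCAE (version 5.0". It then gives the one counting rule: "For laboratory indicators, the maximum toxicity that occurred during the study period is summarized in the form of counts and percentages". The sentence after that sets a baseline comparison for other measures only: "The changes in vital signs and ECOG scores will be compared with baseline levels and carried out descriptive statistics". The paragraph ends by promising a summary over time of vital signs, ECG, laboratory and physical examination, and Section 10 says in general that variables will be described at each observation time. Neither of these gives a counting rule for laboratory grades.

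Section 8.1 lists the matching endpoint, again without a baseline term: "Safety laboratory inspections classified according to NCI-CTCAE (version 5.0".

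Two eligibility rules in Section 4.1 matter here. Criterion 4 makes every patient pre-treated: "Refractory and relapsed ENKTCL that has failed the treatment of asparaginase-based chemotherapy or radiochemotherapy". Criterion 11 admits patients once the toxicity of earlier treatment "has recovered to the grade 1 level or baseline level according to Common Terminology Criteria for Adverse Events".

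Among the things that Section 8.2.1 says are not adverse events is: "Pre-existing disease or condition at the beginning of the study, with predictable fluctuations that did not aggravate during the study period".

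**The concern.** The label and the rule do not match. A change needs two values, one before treatment and one after. A maximum grade needs only one, and takes no account of where the patient started. In a pre-treated population that may enter with residual grade 1 toxicity, a patient who starts at grade 1 and stays there has changed by nothing, yet has a maximum of grade 1.

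This matters because CTCAE-graded laboratory results are a listed safety endpoint, and Section 5.7 names falls in platelets, white cells or neutrophils, and haemoglobin among the common reactions to chidamide. The trial has one arm, so no control group shows how many such abnormalities would be present anyway. Low-grade rates in this table could mix drug effect with entry status.

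**Working it through.** The plan states no figure on this point, so there is nothing to reproduce. The check sets the rule against the entry conditions and follows single patients through it.

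**1. Can a graded abnormality be present at entry?** Yes. Criterion 11 allows grade 1 or baseline-level residual toxicity. Exclusion criterion 6 then caps toxicity from earlier anti-tumour treatment at grade 1, apart from hair loss and pigmentation, so this route supports grade 1 at entry and no more. With marrow involvement, criterion 8 also admits platelets from 50 and neutrophils from 1.0 × 10⁹/L. Section 5.9 requires 75 and 1.5 × 10⁹/L before chidamide resumes after a grade 3 or 4 event, so some patients may start below the protocol's own recovery levels. The documents do not give the low-grade CTCAE cut-offs for blood counts, so these values cannot be turned into grades from the text.

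**2. Can an unchanged entry value reach grade 3 or 4?** For neutrophils, no: Section 5.9 puts grade 3–4 below 1.0 × 10⁹/L, and eligibility requires at least 1.0.

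**3. Does the wording on the study period remove the problem?** No. Section 8.1 starts safety monitoring at consent, while the Synopsis dates subject duration from first dose. Even if only post-dose samples enter the maximum, an unchanged abnormality is found again in the sample before cycle 2.

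**4. Two patients under the two rules, for one parameter:**

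| | Grade before first dose | Worst grade after | Literal maximum rule | Rise above baseline |
|---|---|---|---|---|
| Patient A | 1 | 1 | counted | not counted |
| Patient B | 0 | 1 | counted | counted |

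The maximum-grade table gives A and B the same entry.

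**5. Size per patient.** Each patient like A adds 1/n to the rate for that parameter. Phase II has n = 28 (Sections 5.1.2 and 10.1): 1/28 = 3.6 percentage points. Over both phases Section 10.1 gives 37 to 46 patients: 1/37 = 2.7 and 1/46 = 2.2 points.

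**6. Total size.** If a share b of patients enters with a graded abnormality and a share w of those worsens on treatment, the excess is b × (1 − w). The documents give neither b nor w, so the total cannot be determined.

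**7. Is the baseline grade available?** Yes. The Schedule of assessments marks routine blood tests at screening and at every cycle including the first, with a note placing them 2 to 0 days before each cycle.

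**The case against.** The best defence is that the two sentences should be read together. The summary is announced as one of changes, and a stable pre-entry value is not naturally a toxicity that occurred during the study. That benign reading is available, and this is why the point holds only for the literal reading. It does not settle the matter, because criterion 11 uses the word toxicity for what patients bring with them, and a programmer handed the counting sentence could implement it as written.

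Second, the information is not lost. The chronological summary and the per-visit description will show pre-dose values, and Section 8.2.3 already refers to worsening from baseline when laboratory findings are reported as adverse events. This stands, and it limits the consequence. What those summaries do not do is pair each patient's worst grade with that patient's own starting grade.

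Third, shift tables are commonly left to a statistical analysis plan, which is not at hand. That is right, and the absence of such a table is not the finding. The finding is a rule that the protocol does state under a label that the rule does not meet.

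Two stronger readings are tempting. A reader might infer a contradiction with Section 8.2.1, because a stable low count is left out of the adverse event table and counted in the laboratory table. The two tables serve different purposes and need not agree, so this is a difference to explain, not a contradiction. A reader might also infer a large inflation. With assumed values of b = 10% and w = 75% the excess is 0.10 × 0.25 = 2.5 points; with b = 30% and w = 25% it is 0.30 × 0.75 = 22.5 points; with b = 0 it is nil. That spread only reflects the chosen inputs, and nothing in the protocol supports one value over another.

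**Conclusion.** The point holds as a minor one. Section 10.3 promises changes and defines a level; taken literally, its rule counts entry abnormalities that do not move on treatment. As far as the documents show, the effect is limited to low-grade entries in a single descriptive table. It does not reach adverse event reporting, the response endpoint, the sample size or the dose-limiting toxicity rules. The only size the documents support is 3.6 percentage points per affected patient in phase II; how many patients are affected is unknown. The conclusion rests on the literal reading of the counting sentence and on criterion 11 admitting residual grade 1 toxicity. It does not rest on the marrow-involvement thresholds or on the liver-test limits, which cannot be converted to low CTCAE grades from the text.

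**What to change.** In Section 10.3, replace the counting sentence with one that summarises, for each laboratory parameter, the worst CTCAE grade after first dose against the baseline grade, with baseline defined as the last value before first dose. State that a laboratory toxicity counts as treatment-emergent only when the grade rises above baseline.

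No new sample or visit is needed, since blood is already drawn before cycle 1. The cost is a sentence in the protocol, one more table, and reported low-grade laboratory toxicity rates that will be slightly lower than under the maximum-grade rule.

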#### **10.4 Efficacy analysis**

The researcher can decide the patient's treatment plan based on the efficacy assessment made by the research center. Please refer to Chapter 7.1 for the definition of each efficacy endpoint. The confirmed ORR and the 95% Clopper Pearson confidence interval should be calculated. In addition, other efficacy endpoints, including PFS, DCR, DoR and OS should also be evaluated.

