| Sample Size:                             | Approximately 37-40 patients.                                                                                                                                                                                                                                                                                                                                                                                                                                                                                                                                                                                                                                                                                                                                                                                                                               |
| Statistical analysis                     | 
Study Hypotheses:
 
 
• ORR based on investigators for patients treated with sintilimab plus chidamide to be 80% with a one-sided type 1 error rate of 5% and at least 80% power.
 
• Simon's two-stage design was used.
 
• Sample size for phase II of the study was calculated assuming the target ORR of combination treatment to be 80% with a one-sided type 1 error
 
                                                                                                                                                                                                                                                                                                                                                                                                        |

|  |                                                                                                                                                                                                                                                                                                                                                                                         |

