|--|-----------------------------------------------------------------------------------------------------------------------------------------------------------------------------------------------------------------------------------------------------------------------------------------------------------------------------------------------------------------------------------------|
|  | 
rate of 5% and at least 80% power.
 

• ORRs were reported with two-sided 95% exact confidence intervals (CIs), and the number and percentage of patients in each response category were descriptively tabulated. DOR, PFS, RFS, and OS will be analyzed by Kaplan-Meier approach. Safety analyses will be presented descriptively.

 |
|--|-----------------------------------------------------------------------------------------------------------------------------------------------------------------------------------------------------------------------------------------------------------------------------------------------------------------------------------------------------------------------------------------|

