**Approximately 9 to 18 patients are needed for stage Ib.**

- The phase II study adopts the Simon two-stage optimal design method. The main purpose of the research is to use the maximum tolerated dose determined in phase Ib as the recommended dose to preliminarily evaluate the ORR of treatment of chidamide combined with anti-PD-1 antibody in the treatment of refractory and relapsed Extranodal NK/T-cell lymphoma. According to previous studies,  $P_1$  is supposed as 0.8 (expected effective rate) and  $P_0$  as 0.55 (poor effective rate), with  $\alpha=0.05$  and  $\beta=0.8$ . The best two-stage design is (4/7, 19/28). That is, 7 patients were enrolled in the first stage, and if only 4 or fewer patients were effective, the trial was terminated. Otherwise, the trial enters the second phase and 21 more patients will be enrolled. That is, a total of 28 patients will be enrolled in the phase II study. A total of 37 to 46 patients will be enrolled in stage Ib and II. The study loss rate was set at 10% and a total of 40-50 patients will be enrolled. If the number of effective cases in all patients in the two stages exceeds 19, there is an 80% probability that the test drug is effective.

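### At exactly 20 of 28 responders the two-stage count rule declares success while the planned two-sided 95% Clopper-Pearson interval still contains the 55% null

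*Protocol*

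**What the plan says.** On the design, section 10.1 states: "The phase II study adopts the Simon two-stage optimal design method". The null is given "as 0.55 (poor effective rate") and the target "is supposed as 0.8 (expected effective rate"). It continues: "The best two-stage design is (4/7, 19/28"). At the first stage, "if only 4 or fewer patients were effective, the trial was terminated". The drug is called effective if responders over both stages exceed 19, that is, at 20 or more of 28. The synopsis gives the test level: "with a one-sided type 1 error rate of 5% and at least 80% power".

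On reporting, the synopsis says "ORRs were reported with two-sided 95% exact confidence intervals (CIs"), and section 10.4 names the method: "The confirmed ORR and the 95% Clopper Pearson confidence interval should be calculated".

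The protocol does not adjust this interval for the two stages or tie its level to the one-sided 5% test. It does not say which result governs if the interval and the count rule differ. Separately, the synopsis (Study Design) stops the first stage only when fewer than 4 of 7 respond, whereas section 10.1 also stops at exactly 4.

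**The concern.** The decision and the interval differ in two ways. The test spends 5% in one tail, while the interval allows 2.5% per tail. The test also accounts for the chance to stop after 7 patients, while Clopper-Pearson treats all 28 as one sample. Where two such procedures differ, an outcome near the boundary can pass one and not the other.

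A trial that met its own success criterion could then be published with a primary-endpoint interval containing the rate the protocol calls poor. An interval or p-value method chosen after seeing that result would look data-driven. Section 10 adds to the exposure by setting a general significance criterion of p at or below 0.05 without tying it to the two-stage rule.

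**Working it through.** **Inputs.** p0 = 0.55, p1 = 0.80, first stage 7 patients (stop at 4 or fewer responders), total 28 with success at 20 or more: all section 10.1. One-sided 5% and power of at least 80%: synopsis (section 10.1 writes beta = 0.8, which only makes sense as power). Interval method: section 10.4 and synopsis. The interval is taken on the 28 phase II patients.

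**1. Reproduce the design.** Let Y1 ~ Bin(7, p), Y2 ~ Bin(21, p), and

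T(x, p) = sum over y = 5, 6, 7 of P(Y1 = y) × P(Y2 ≥ x − y),

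the probability of passing stage 1 and reaching at least x responders.

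- T(20, 0.55) = 0.2140×0.0964 + 0.0872×0.1971 + 0.0152×0.3413 = 0.0206 + 0.0172 + 0.0052 = 0.0430.
- T(20, 0.80) = 0.2753×0.8915 + 0.3670×0.9569 + 0.2097×0.9856 = 0.2454 + 0.3512 + 0.2067 = 0.8033.

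An exhaustive search over total sizes 10 to 39 returns (4/7, 19/28) as the optimal design, with expected size 7 + (1 − 0.684)×21 = 13.6 under 55%. The stated design is correct.

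**2. The planned interval at the boundary.** The Clopper-Pearson limits for x of n are the beta quantiles B(0.025; x, n−x+1) and B(0.975; x+1, n−x).

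- 20/28 (71.4%): 51.3% to 86.8%, which includes 55%.
- 21/28 (75.0%): 55.1% to 89.3%, which excludes 55%.

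So 20 is the only successful count at which rule and interval disagree.

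**3. Which mismatch causes it.** Lower limits at 20/28:

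| Method | Two-sided 95% | Two-sided 90% |
|---|---|---|
| Fixed sample (Clopper-Pearson) | 51.3% | 54.3% |
| Two-stage exact | 52.6% (T(20, p) = 0.025) | 55.7% (T(20, p) = 0.05) |

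Only the limit that corrects both level and design excludes 55%. The one-sided p-values show the same: 0.058 as a fixed sample of 28, 0.043 under the two-stage rule. The upper end of the two-stage 90% interval solves 1 − T(21, p) = 0.05 and is 88.1%.

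**4. How often.** P(exactly 20 after passing stage 1) = T(20, p) − T(21, p).

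- ORR 80%: 0.8033 − 0.7396 = 0.064, or 8% of successes (0.0637/0.8033).
- ORR 70%: 0.4237 − 0.3108 = 0.113.
- ORR 55%: 0.0430 − 0.0197 = 0.023, or 54% of false positives (0.0233/0.0430).

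**5. Does the Clopper-Pearson interval lose coverage?** Coverage was summed over all outcomes, with n = 7 if stopped and n = 28 otherwise. It is 97.6% at ORR 55%, 97.7% at 70% and 97.4% at 80%, and at least 95.2% at every whole percentage from 5% to 95%. A grid in steps of 0.05 points finds one sliver, about 81.59% to 81.65%, where it dips to 94.0%: the upper limit for 3/7 (81.59%) has just fallen below the truth while the lower limit for 27/28 (81.65%) still lies above it. On that grid the lower limit exceeds the true ORR with probability at most 2.5%, and 2.0% at 55%.

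**6. Under the synopsis stopping rule.** Letting y run from 4 to 7 in T gives alpha 0.0544 and power 0.8915 for the same cut-off. The two-stage 90% lower limit at 20/28 becomes 54.6%, which no longer excludes 55%.

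**The case against.** The strongest reply is that the protocol never makes the interval the test. Success is a responder count with exact alpha 0.043 and power 0.803. The synopsis mentions the interval as reporting, in the same sentence as descriptive tabulation. A two-sided 95% interval beside a one-sided 5% test is the stricter report and cannot favour the drug. One outcome is affected, and estimation detail often sits in a statistical analysis plan. Most of this stands and limits the weight of the point. It does not remove it: the protocol itself fixes the interval's method and level, and that choice can disagree with its own rule.

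A reader might infer more, in three ways that the documents do not support.

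- That the interval is invalid under a Simon design. Step 5 shows otherwise: apart from a negligible sliver it is conservative.
- That power really is 74.0%, the chance of 21 or more responders at ORR 80%. That would follow only if excluding 55% from the interval were the success criterion, and section 10.1 makes it the count.
- That the observed proportion is biased downward and should give way to the UMVUE. Over all trials its mean is 77.0% at a true 80% and 49.8% at a true 55%. Among trials reaching stage 2, the only ones that can succeed, the means are 81.2% and 60.4%, so the bias is upward. The UMVUE is 79.5% at an observed 71.4% (20/28) and 78.3% at a failing 67.9% (19/28). Making it the headline would show a barely passing trial almost at its 80% target.

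**Conclusion.** The point holds as a mismatch of modest size between the decision and the reported interval. It is not a wrong test, a loss of power or an invalid interval. It bites at exactly 20 responders and nowhere else among successful results. It is worth fixing because it concerns the primary endpoint, the correction is cheap, and it must be settled before the data are seen.

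The two-stage figures assume the section 10.1 stopping rule and an analysis of exactly 28 phase II patients. The agreement at 55.7% is lost under the synopsis rule, where the cut-off also exceeds 5% alpha.

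**What to change.** First reconcile the first-stage stopping rule between the synopsis and section 10.1, and recompute alpha and the matched interval under the rule that is kept.

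Then, in section 10.4 and the synopsis:

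- State that the more-than-19-of-28 rule governs the efficacy conclusion.
- Add a two-stage design-based exact two-sided 90% confidence interval as the one matching the one-sided 5% test.
- Keep the observed ORR with its 95% Clopper-Pearson interval, labelled descriptive. A UMVUE may be given as a supplementary estimate but should not replace the observed ORR.

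The cost is a few lines of code and one extra interval to explain. No new data or patients are needed.
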